### Study interventions

#### Intervention layout

The intervention is inspired by a Norwegian community-based intervention study for adults in the chronic stage of TBI [44], which in turn was modeled after a study by Winter and colleagues [45]. Several alterations were made to adapt the intervention to children and families, e.g., including schools and Statped (the Norwegian Service for Special Needs Education) in establishing and following up school-related strategies and including a parent seminar. A flowchart of the study is presented in Fig. 2.

**Fig. 2 Fig2:**
[figure not shown]
Flowchart of the CICI study

The intervention lasts for approximately 6 months and consists of 12 sessions, whereof most will be videoconferences, with the possibility of one to two home sessions. Seven 1.5- to 2-h family sessions make up the largest part of the intervention. They will be delivered approximately every 2 to 3 weeks. During the intervention, parents will participate in a 1-day seminar with psychoeducation and experience sharing. For practical reasons, parent seminars will be held in small groups and on fixed dates. One classroom observation will be carried out by a special needs educator before the first of four school sessions, which will be held as three videoconferences and one phone call during the same 6 months as the family sessions and the parent seminar. School sessions will be delivered with longer intervals between family sessions. The last family session marks the end of the intervention.

School and family sessions might be conducted in person to accommodate the family’s specific needs, if feasible according to local COVID-19 restrictions and geographical location. Figure 3 provides an overview of the intervention.

**Fig. 3 Fig3:**
[figure not shown]
Overview of the intervention sessions

### Intervention content

#### Family sessions

Families in the intervention group will, in collaboration with their therapist, establish approximately one to five SMART goals during family sessions. SMART goals will be a main focus in the family sessions and will often, but not always, be based on the target outcome areas (the family’s main pABI-related problems in daily life), depending on the wishes and needs of the family. SMART goals are Specific, Measurable, Achievable, Realistic/Relevant, and Timed [63]. For a quantifiable measure at the end of the intervention (family session 7), goal attainment scaling (GAS) [64] will be applied during goal setting. Current recommendations for the use of GAS will be followed [65]; however, for motivational purposes for the children, a scaling from 1 to 5 will be presented, instead of −2 to 2. Appropriate treatment strategies will be discussed and defined for every SMART goal. Families will be encouraged to actively apply the strategies in daily life during the intervention period. Experiences with the strategies will be discussed during sessions and strategies revised when necessary, but the goals and GAS will not be changed after they have been defined. As the literature on treatment of ABI-related challenges in children in the chronic phase is scarce [6], the intervention strategies will rely on the available evidence-based recommendations existing for the pediatric population [8, 27–30] as well as the evidence-based recommendations given to the adult population, with age-appropriate adaptations (i.e., Translating Evidence-Based Recommendations into Practice [66]). In addition, therapists will draw from the literature on children with neurodevelopmental disorders and typically developing children when choosing rehabilitation strategies, as suggested by Slomine and colleagues [5]. A psychoeducational booklet with a biopsychosocial framework, authored by therapists with long experience from working with children with ABI, will be provided to all participants in the intervention group, including teachers. The topics for the booklet were selected based on recent research about the needs of children with ABI [47] and relevant topics for parents were added. Users contributed feedback during the development of the booklet. The booklet includes the following chapters with information, advice, and links to useful Internet sites: common sequelae after pABI, cognitive difficulties, emotion regulation, social functioning, fatigue, sleep, pain management, psychological well-being, stress management, communication, parenting a child with ABI, and identity after pABI. Relevant topics from the booklet will be discussed during sessions. Children contribute to the extent they are able to. Care is taken to include the children in the goal-related work as much as their age and cognitive skills allow, to motivate them to share their experiences with the strategies and to take part in adapting strategies that do not work as well as intended. No concomitant care or treatment is prohibited or will be retracted during the trial.

#### School sessions

While the SMART goals are defined by the families in collaboration with the therapist, relevant school-related strategies to reach the goals will also be defined, closely monitored and, when necessary, revised in school sessions. Thus, schools will be expected to apply the established goal strategies during the intervention period. For instance, the goal for a child with fatigue to reduce tantrums at home cannot be solved by the family alone, but also requires that the school and teachers understand fatigue and provide an environment where the child can learn and interact with peers without exhausting himself/herself. As an example, appropriate school strategies for fatigue may include noise reduction in the classroom, extra breaks for the child during the day, extra time to complete tasks, and information to classmates to enhance understanding and reduce hurtful comments. In addition to working with the strategies, teachers will receive psychoeducation about pediatric brain injury within a biopsychosocial framework. Parents will be encouraged to participate in school sessions to optimize home-school collaboration. Children are welcome to participate in school sessions if they wish to. Primary health care providers will be invited to attend school sessions when relevant.

#### Parent seminar

In line with recent studies that highlight the importance of including the children’s caregivers in the rehabilitation process [6], and the need to discuss certain topics without children present, a day-long parent seminar targeting family functioning and parenting will be delivered. Topics for the parent seminar include parents’ experiences from working with SMART goals and strategies; parenting after pABI with a particular focus on communication; changes in family dynamics and caring for siblings after pABI; emotional reactions of the family after pABI with a particular focus on feelings of guilt, grief, and embarrassment; and self-care. The topics will be followed up in family sessions if relevant to the goals set. The parent seminar is inspired by interventions carried out in studies recommended in several Cochrane reviews [38, 67–72]. To heighten user involvement, a member of the user organization who has a child with ABI will be invited to participate in parent seminars.

#### Collaboration with local health care professionals

When families wish to invite health care professionals in the municipality with whom they already have established contact to collaborate in the study, these will be asked to participate in some of the intervention sessions, depending on the goals set. Involvement of local resources, including schools, will ensure knowledge transfer from specialized health care to the community. For families who lack help from local health care professionals, the therapists will refer the child to a specialist or support the family in seeking relevant help if judged beneficial. The CICI study will keep track of participation of health care professionals in CICI sessions.

#### Therapists in the CICI study

Three experienced therapists, two neuropsychologists and one pediatric nurse, will deliver the intervention, in close collaboration with an experienced special needs educator who will be in charge of the school sessions. To ensure equal quality of interventions, the three therapists will collaborate closely and frequently discuss SMART goals, goal attainment scaling, and relevant strategies for the goals with each other and with senior researchers. The research group consists of experienced health personnel, and the study has established procedures to deal with unexpected adverse events or medical/psychological issues in acute need of treatment. In such cases, participants will be referred accordingly.

#### Treatment as usual

Children in the control group will receive their usual health care and rehabilitation services (TAU). In Norway, health care in the chronic phase of ABI is largely provided by the municipalities, in cooperation with the specialist health care system. As the provided rehabilitation varies greatly depending on the needs of the children and on the municipalities involved, parents will be interviewed at all time points about the type and amount of health care services provided for each child participant in both groups. This will enable a comparison of service provision between the groups regarding frequency, duration, and profession of the health care professionals involved.

#### Technical solutions and data management

The videoconference solution is provided by the Norwegian Health Net (join.nhn.no) and is delivered by Pexip. It is encrypted and pin codes are used to access virtual meeting rooms, which are locked after all participants have joined. Therapists will use their work computers with an integrated camera and participants use their own computer or tablet with an integrated camera. Laptops can be lent to participants if they do not have a technical device that is suited for videoconferences. To optimize sound, therapists will use USB speakerphones and will lend speakerphones to participants if the sound is judged suboptimal during session 1. The videoconference solution is risk assessed and approved for clinical use by Sunnaas Rehabilitation Hospital. Procedures for clinical use are developed and therapists received training prior to the intervention.

Questionnaires will be sent to participants using Viedoc, a secure electronic data catching system developed for clinical trials. Its homepage cannot be googled but must be accessed with the correct Web address. Every participant will get his/her own username and password to use on their own smartphone, tablet, or computer. The questionnaires will be available in Viedoc for a limited amount of time for each time point and every participant can complete a questionnaire only once. Questionnaires are not visible for people who are not logged in and cannot be printed from Viedoc.

To ensure that the data set is as complete as possible, the therapists will in turn be assigned administrative responsibility of follow-ups of all participants and a scientist will be hired to assist.

Deidentified quantitative data will be stored in Viedoc while recruitment is ongoing and the database on the research server at Sunnaas Rehabilitation Hospital during the latest stage of the study. The qualitative data (the audio recordings of the interviews) will be stored in controlled access folders on the same research server. Tapes and transcripts will be kept locked at Sunnaas Rehabilitation Hospital. All data will be securely contained for 5 years after the end of the project, on the electronic research server at Sunnaas rehabilitation hospital, with restricted access limited to the research group. Deidentified individual clinical trial participant-level data (IPD) will not be shared publicly due to privacy regulations. Important protocol modifications will be reported to the Norwegian Regional Committee for Medical and Health Research Ethics and amendments will be made to the trial registry (Clinicaltrials.gov).

#### Statistical analyses

Descriptive statistics will be used to depict demographics, insult characteristics, and service delivery at baseline as well as acceptability in the intervention group.

Data will be analyzed with linear mixed models taking into account the repeated measures design of the study. All assessment points will be included in the analyses. The main effect of time, treatment, and the interaction between time and treatment will be assessed. The main endpoint for the primary outcome is at T3 (9-month follow-up). The analysis of primary interest in establishing treatment efficacy is a time × group interaction in the direction of the intervention group improving above the levels of the control group at T3. Estimates of mean between-group changes from T1 to T2 and T2 to T3 will also be provided. For primary outcomes, an alpha level of *p* < 0.025 will be applied, as there are two primary outcome measures. A mixed model analysis uses all the available data to compensate for the missing data points. Thus, imputation techniques are not necessary.

Additional analyses including subgroup analyses will be performed, e.g., to compare the effect of the intervention on parent- and child-reported outcomes and outcomes reported by different caregivers (e.g., mothers and fathers). *T*-test analyses will be used for between-group mean comparisons for normally distributed continuous data, and Mann-Whitney *U*-tests for skewed data. Kruskal-Wallis *H* will be used when more than two groups are compared. Individual and treatment-related predictors for goal attainment will be assessed by multivariable regression analysis in the intervention group.

An intention to treat model will be followed, using data from all randomized participants, regardless of whether they complete the intervention or not.

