### Randomization and allocation concealment

Participants will be randomly allocated in a 1:1 ratio to either the intervention group or the control group after completing the baseline (T1) assessment. A Web-based block randomization will be generated by an independent statistician prior to trial start-up to ensure randomization and complete allocation concealment. The allocation will be performed in Viedoc™ (Viedoc Technologies AB, Uppsala, Sweden), the electronic data capture system used in this study (see below). The allocation sequence can be accessed by neither the therapists nor the outcome assessors, only by the study principal investigator. Randomly generated block sizes will be applied. Outcome assessors blinded to group allocation will interview participants and collect information on target outcome areas (main pABI-related problems in daily life) at T2 and T3. For apparent reasons, blinding of participants and interventionists is not possible, but researchers will be blinded to group allocation in the final database, as the participants will be provided with new ID numbers.

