#### Sample size and power calculations

As the precise prevalence and incidence of pABI in Norway is not known, we have established eligibility estimates based on Norwegian and international research regarding the largest subgroups to estimate. In the greater Oslo region (South-Eastern health region), an estimated 105 children per year acquire a brain injury or insult: approximately 35 acquire a TBI (mild TBI not verified by CT or MRI excluded) [73, 74] approximately 22 suffer from cancer in the central nervous system [75], approximately 48 children receive a diagnosis of encephalitis [76, 77], and approximately 18 children experience a stroke each year (perinatal stroke excluded) [78]. About one-third of the surviving children are expected to experience unmet health care needs more than 1 year after injury/insult [79, 80]. Thus, with a rough estimate of 30 eligible children per year in the Oslo region, recruitment for 2 years, including recruitment of children whose injury/insult happened during the last 15 years, the number of eligible families should be sufficient to allow recruitment of 70 families. With an estimated attrition rate of 5–10%, based on our earlier TBI research, around 64 participants are expected to complete all outcome assessments, with 32 children in each intervention arm. Children will be recruited from Sunnaas Rehabilitation Hospital, Oslo University Hospital, Statped (the Norwegian Service for Special Needs Education), and through user organizations.

Effect size and power calculations were conducted using G*Power [81]. Since there are two primary outcomes, the calculation was conducted with an alpha level of 0.025. Two-sided *t*-tests were used as the basis for the analysis. With a statistical power of 0.8 and a sample size 70 (expected *N* = 64 after attrition), we will have an 80% chance of detecting treatment effects of 0.8 (Cohen’s *d*). Results from the feasibility study indicated the measures to be sensitive to the CICI intervention, and a recent RCT [82] which studied the effects of a less intensive and less complex intervention for children with mild brain injury, found an effect on symptoms reported on the HBI, with very large effect sizes. We are not aware of pediatric studies that are directly comparable to the current study.

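### The primary mixed model leaves the T1 difference between arms free, so its T3 contrast is valid but less precise than one that uses randomisation after baseline

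*Protocol article*

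**What the plan says.** Under Statistical analyses, the protocol article plans a linear mixed model in which all three assessments (T1, T2, T3) are used. On its terms it says: "The main effect of time, treatment, and the interaction between time and treatment will be assessed". The result that decides efficacy is the time by group interaction at T3, tested at 0.025 for each of the two primary outcomes. Neither a common T1 mean nor a baseline covariate is mentioned.

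Under Randomization and allocation concealment, families are allocated 1:1 "after completing the baseline (T1) assessment".

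Under Sample size and power calculations, "the calculation was conducted with an alpha level of 0.025" and "Two-sided *t*-tests were used as the basis for the analysis". The result is that, with 64 of 70 families completing, "we will have an 80% chance of detecting treatment effects of 0.8" (Cohen's d). The section does not say whether the SD behind d is that of the T3 score or of the change from T1, and it gives no correlation between assessments.

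**The concern.** When T1 is one of the outcomes and the model has both a treatment main effect and a time by treatment interaction, the main effect absorbs whatever difference the arms show at T1. The T3 interaction is then the T3 difference minus the T1 difference, that is, a difference in mean change.

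Because T1 precedes randomisation, the T1 difference is chance alone. Subtracting it in full brings its sampling error into the treatment estimate. It also over-corrects: for a given chance imbalance at T1, the change contrast is off by (1 - rho) times that imbalance. With 32 per arm the standard error of the T1 difference is sqrt(2/32) = 0.25 SD, so imbalances of that order are to be expected.

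The trial is powered only for a large effect, and the Limitations section says that the number of available participants restricts its size. Precision gained through the analysis is therefore worth having.

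**Working it through.** **Inputs from the protocol article.** Two-sided alpha 0.025; power 0.80; d = 0.8; 70 randomised; "around 64 participants are expected to complete all outcome assessments, with 32 children in each intervention arm"; 1:1 allocation.

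**Assumptions.** The T1-T3 correlation rho is not given, so 0.3, 0.5 and 0.7 are used. SDs are equal at T1 and T3, time is categorical and data are complete. For the power columns only, d is taken in units of the T3 SD.

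**Step 1: the article's own figure.** For a two-sample t-test with 32 per arm, df = 62 and the noncentrality is 0.8 × sqrt(32/2) = 3.2. Exact power is 81.4%, and the detectable d at 80% power is 0.787. The smallest sufficient size is 31 per arm, or 62 in all; 62/0.90 = 68.9, so 69 families, against 70 planned. The stated 80% reproduces.

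**Step 2: variances.** With the T3 variance set to 1, the residual variance behind each contrast is:
- planned contrast (free T1 means, difference in change): 2(1 - rho)
- T1 means constrained equal, or T1 as covariate: 1 - rho²

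The ratio of the second to the first is (1 - rho)(1 + rho) / [2(1 - rho)] = (1 + rho)/2. It is below 1 for every rho below 1. This ratio does not depend on which SD the d of 0.8 uses.

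**Step 3: power at d = 0.8 (T3-SD units) and detectable d at 80% power.** The noncentrality of 3.2 is divided by sqrt(2(1 - rho)) or sqrt(1 - rho²); the adjusted analysis loses one further df.

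| rho | Planned: power (detectable d) | Constrained or adjusted: power (detectable d) | Variance ratio (1+rho)/2 |
|---|---|---|---|
| 0.3 | 65.8% (0.93) | 85.2% (0.75) | 0.65 |
| 0.5 | 81.4% (0.79) | 91.6% (0.68) | 0.75 |
| 0.7 | 96.4% (0.61) | 98.4% (0.56) | 0.85 |

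The variance is thus 35%, 25% and 15% lower. At rho 0.5, 64 completers analysed by change carry about the information of 64 × 0.75 = 48 analysed with baseline adjustment.

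**Step 4: simulation check.** With 20,000 simulated trials per setting, the change contrast and the baseline-adjusted contrast had power of 66.1% and 84.9% (rho 0.3), 81.5% and 91.3% (0.5), and 96.5% and 98.3% (0.7). With no treatment effect, both rejected in about 2.5% of trials. The planned test therefore holds its level.

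**Step 5: where the planned contrast would fall below 80%.** In T3-SD units this needs 2(1 - rho) > (0.8/0.787)², about 1.034, so rho below about 0.48. Above rho 0.5 the planned contrast has more power than the plain T3 t-test. In change-SD units, a t-test on change is the matching calculation and gives 81.4% at any rho.

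**The case against.** The strongest reply is that nothing here is an error. The free-baseline contrast is unbiased over randomisation and holds its type I error, the 80% figure reproduces, and the article openly sets out to estimate between-group changes. All of that stands. It makes this an improvement to a sound analysis, not the repair of an invalid one.

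A reader might go further and infer that the planned model has less than the stated 80% power, or that it does not match the t-test used for sample size. The article does not support either. It leaves the SD behind d = 0.8 open: in change-SD units the t-test fits the planned contrast, and in T3-SD units there is a shortfall only for rho below about 0.48. The 65.8% at rho 0.3 depends on an assumed correlation. At rho 0.7 the planned contrast has 96.4% power and the gain is only 2 percentage points.

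It can also be said that baseline parametrisation belongs in an analysis plan that is not shown. That does not dispose of the point, because the article itself names the model terms and the deciding contrast, and those terms most naturally mean a free T1 difference. Time coding and covariance structure may well be left to such a plan, which is why categorical time is listed as an assumption.

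**Conclusion.** The point holds as one of efficiency. The primary contrast as described is a difference in change from T1 and does not use the fact that the arms share one T1 mean by design. Under the assumptions listed, its variance is 2/(1+rho) times that of the constrained or adjusted contrast: 1.54, 1.33 and 1.18 times at rho 0.3, 0.5 and 0.7. The direction is the same at every rho below 1; the size depends on a correlation that the article does not give. The planned test remains valid, and the sample size statement is not shown to be wrong.

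**What to change.** In the analysis section or analysis plan, state that T1, T2 and T3 are outcomes with the T1 mean constrained equal across arms: time effects, treatment × T2 and treatment × T3, no treatment effect at T1, and an unstructured covariance. Name the T3 treatment contrast as the primary estimate for each primary outcome. This keeps every randomised family, in line with the intention-to-treat statement.

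A model of T2 and T3 with T1 as covariate, with a slope allowed to differ by time, is a close alternative. It is not fully equivalent, because it drops families with only a T1 score.

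When power is restated, say which SD the d of 0.8 refers to and which rho is assumed. In T3-SD units the detectable d becomes about 0.79 × sqrt(1 - rho²), which gives at least 80% power at d = 0.8 for any rho of 0 or more.

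The cost is a few sentences. Data collection, sample size and the T3 endpoint do not change.

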**Methods:**

Children aged 6–16 years with MRI/CT-verified intracranial abnormalities will be included in the CICI study if they have persistent self- or parent-reported cognitive, emotional, and/or behavioral challenges 1 year or more after insult and attend school regularly. A total of 70 families will be randomized 1:1 to an intervention or a control group. The intervention consists of seven family sessions, one parent seminar, and four school sessions delivered over approximately 6 months. The parent seminar will be held in person, and the other sessions will mainly be video based. The children’s and families’ self-reported major challenges in everyday life will be targeted using SMART goals. Evidence-based strategies, when available, will be applied to achieve the goals, combined with psychoeducation. Goal attainment scaling (GAS) will be used to evaluate goal attainment. Data is collected at baseline and after approximately 6 and 9 months. External assessors are blinded to group allocation. Primary outcomes are parent-reported brain injury symptoms in children and parenting self-efficacy at 9 months of follow-up. Secondary outcomes include child-reported brain injury symptoms, quality of life, executive functioning in daily life, parent emotional symptoms, family functioning, and unmet family health care needs. A process evaluation will be conducted.

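### Testing each of the two primary outcomes at a fixed 0.025 is valid, but Holm's step-down rule would give more power for the second outcome at the same 5% family-wise error

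*Protocol article*

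**What the plan says.** The abstract names two primary outcomes at one time point: "Primary outcomes are parent-reported brain injury symptoms in children and parenting self-efficacy at 9 months of follow-up". Under Statistical analyses, the protocol article fixes the threshold for each: "0.025 will be applied, as there are two primary outcome measures". The section Sample size and power calculations uses the same level: "Since there are two primary outcomes, the calculation was conducted with an alpha level of 0.025". It adds "Two-sided *t*-tests were used as the basis for the analysis" and concludes that "we will have an 80% chance of detecting treatment effects of 0.8" (Cohen's d), with 70 families randomized and "around 64 participants are expected to complete all outcome assessments, with 32 children in each intervention arm".

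This is an equal Bonferroni split of 5%, although the article does not use the name. The article states no step-down, ordered or alpha-passing rule. Under Objectives and hypotheses, lower child symptom severity (H1) and better parental self-efficacy (H2) are listed as separate expectations.

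**The concern.** Under the stated rule an outcome must reach 0.025 even when the other primary outcome has already succeeded. Closed testing does not require that. Once one of two hypotheses has been rejected at 0.025, the other may be tested at 0.05 without the family-wise error exceeding 5%.

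Suppose HBI gave p = 0.01 and TOPSE p = 0.04. The stated rule would leave H2 unestablished, while Holm would establish both hypotheses at the same 5% family-wise level.

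This matters because the trial is sized for large effects only, and the Limitations section says that available participants and the timeframe restrict the sample. More families are hard to find. A better testing rule needs none.

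**Working it through.** **Inputs.** From the protocol article: two primary outcomes, 0.025 each, two-sided t-tests, d = 0.8, 1:1 allocation, and 64 completers (32 per arm) out of 70. The stated attrition of 5–10% leaves 70 × 0.90 = 63 to 70 × 0.95 = 66.5, consistent with 64. The article gives no HBI–TOPSE correlation, so a range of 0 to 0.7 is assumed.

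**Reproducing the stated power.** The two-sample t-test has 62 degrees of freedom and noncentrality d·√(n/2) = 0.8 × √16 = 3.2. At two-sided 0.025 the power is 81.4%, in line with the stated 80%. The smallest n per arm that reaches 80% is 31. At two-sided 0.05 the power is 88.3%.

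**Error control under Holm, for any dependence.**
- Both nulls true: a false rejection requires the smaller p-value to be below 0.025. The probability is at most 0.025 + 0.025 = 0.05, as under the present rule.
- One null true: a false rejection requires that outcome's p-value to be below 0.05. The probability is at most 0.05.

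**Independent outcomes, d = 0.8 on both.** Write a = 0.8142 (power at 0.025) and b = 0.8830 (power at 0.05), so b − a = 0.0688.
- Both, fixed 0.025: a² = 0.663.
- Both, Holm: b² − (b − a)² = 0.7797 − 0.0047 = 0.775.
- One given outcome, Holm: a + a(b − a) = 0.8142 + 0.0560 = 0.870.
- At least one, either rule: 1 − (1 − a)² = 0.965.

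**Correlated outcomes, d = 0.8 on both** (simulated t statistics, 400,000 runs per setting; the row for correlation 0 is exact):

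| Correlation | Both: fixed 0.025 → Holm | Per outcome: fixed → Holm | At least one, either rule |
|---|---|---|---|
| 0 | 66.3% → 77.5% | 81.4% → 87.0% | 96.5% |
| 0.3 | 68.8% → 78.8% | 81.4% → 86.5% | 94.2% |
| 0.5 | 70.6% → 79.8% | 81.4% → 86.1% | 92.4% |
| 0.7 | 73.0% → 81.3% | 81.4% → 85.6% | 89.9% |

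**Other effect patterns, correlation 0 to 0.7.**
- d = 0.6 on both: power for both rises from 30–42% to 42–52%, and per outcome from 54% to about 60%.
- d = 0.8 and 0.5: power for the weaker outcome rises from about 39% to 48–49%.
- d = 0.8 and 0: power for the outcome with the effect goes from 81.4% to about 81.6% (at correlation 0: 0.8142 + 0.025 × 0.0688 = 0.816). The false-positive risk for the other rises from about 2.5% to 4.1–4.5% (at correlation 0: 0.025 + 0.8142 × 0.025 = 0.045).
- Both nulls true: the family-wise error is 4.3–5.0% under either rule.

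**Intervals.** Every extra Holm rejection has p between 0.025 and 0.05. If interval and test come from the same model, the 97.5% interval for that outcome therefore includes zero every time Holm adds something. With d = 0.8 on both outcomes, that is 77.5 − 66.3 = 11.2% of trials at correlation 0 and 81.3 − 73.0 = 8.3% at correlation 0.7.

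**The case against.** The strongest reply is that nothing here is broken. The rule is valid, the analysis and sample size sections agree, and the stated power reproduces. Choosing the simpler of two valid procedures is partly a matter of preference, and the fixed split keeps each test aligned with its 97.5% interval. All of this stands, so the point is an efficiency gain.

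Three stronger readings are tempting, and the article supports none of them.
- A reader might infer that the trial needs both outcomes to succeed and is underpowered for that. H1 and H2 are separate expectations. No section makes success depend on both, and the power statement does not refer to joint success.
- A reader might infer that Holm makes a positive trial more likely. The chance of at least one significant primary outcome is identical under the two rules. The gain is confined to the second rejection, and the largest figures assume a real effect on both outcomes.
- A reader might infer that the change costs nothing. When only one null is true, the false-positive risk for that outcome rises, though it stays within 5%. The mismatch with 97.5% intervals occurs every time Holm helps.

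Timing also deserves weight. Recruitment began in April 2021, parents who know their allocation report both primary outcomes, and the principal investigator can access the allocation sequence. Relaxing a primary threshold is defensible only if it is fixed before anyone sees outcome data by group.

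**Conclusion.** The point holds as an inexpensive improvement to a stated rule. Holm rejects everything that the fixed 0.025 rule rejects and sometimes more, at the same 5% family-wise level, and it needs no ordering of the outcomes or assumption about their correlation.

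Where both outcomes truly respond with d of 0.6 or 0.8, the gain in power to establish both is about 8 to 12 percentage points. Where only one responds, there is practically no gain.

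The sizes rest on 32 completers per arm, equal-variance t-tests as in the article's own calculation, and the assumed correlations of 0 to 0.7. The planned mixed model may shift the levels. It does not affect the ordering of the two rules or the family-wise bound, provided each p-value is valid.

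**What to change.** Replace the fixed threshold under Statistical analyses by a rule such as: *The smaller of the two T3 p-values for the primary outcomes is tested at 0.025. If it is significant, the other is tested at 0.05; otherwise testing stops.* The sample size statement at 0.025 can stay, because Holm's first step uses that level.

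Settle interval reporting in the same amendment. One option is to show unadjusted 95% intervals beside the Holm decisions. These can mismatch in the other direction: if neither p-value is below 0.025, an outcome with p between 0.025 and 0.05 has a 95% interval that excludes zero but is not declared significant. The alternative is to keep 97.5% intervals and state that a second-step rejection may have an interval that includes zero. Either way, the report should say that the decision follows Holm and not the displayed interval.

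Make the change before any unblinded look at the data, through the route described under Technical solutions and data management (ethics committee and trial registry). The cost is a short amendment and a note on intervals. Sample size, data collection, endpoints and model are unchanged.
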